### Clustering

The relevant hierarchy of observations is that observations over time are clustered within health-facility. This clustering will be explored in analyses of the effectiveness outcomes using either random effects or robust standard errors for clustering by health facility.

## 9.3 Measures to Adjust for Confounders, Heterogeneity and Autocorrelation

### Confounders

Both pre- and post-implementation surveillance periods will be of sufficient duration to minimise the risk of outlier seasonal and social events on the incidence of vivax malaria. Multivariable models, controlling for known potential confounders such as sex, age, weight, calendar month and seasonality will be used for comparisons of malaria incidence, slide positivity and other indices. For the exploratory outcomes, S1.EE1 and S1.EE2 multivariable linear regression models will be adjusted for known potential confounders, baseline haemoglobin levels and G6PD enzyme activity level.

### **Heterogeneity**

The mixed effects models allow for some heterogeneity in slope and intercept at the health facility level. A visual assessment of heterogeneity of intervention effect according to site characteristics will be performed.

### **Autocorrelation**

Autocorrelation for the segmented mixed-effects regression analyses estimating the effectiveness of the implementation package will be assessed visually by plotting the residuals (difference between observed and model predicted outcome) over time for each model.

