**Table 1 Number of patients with vivax malaria attending the ten study clinics in last 12 months**

| Clinic name     | Country   | Locality               | Estimated total number of P. vivax episodes per year | Estimated maximum recruitment in SCOPE Stage 2 (95%) |
|-----------------|-----------|------------------------|-------------------------------------------------------------|------------------------------------------------------|
| Timika          | Indonesia | Timika, Southern Papua | 3173                                                        | 3014                                                 |
| Bhintuka        | Indonesia | Timika, Southern Papua | 1164                                                        | 1106                                                 |
| Pasar Sentral   | Indonesia | Timika, Southern Papua | 4937                                                        | 4690                                                 |
| Wania           | Indonesia | Timika, Southern Papua | 3681                                                        | 3497                                                 |
| Tanjung Leidong | Indonesia | North Sumatra          | 500                                                         | 475                                                  |
| Hanura          | Indonesia | Lampung                | 450                                                         | 428                                                  |
| Baro            | PNG       | West Sepik             | 417                                                         | 396                                                  |
| Mugil           | PNG       | Madang                 | 1044                                                        | 992                                                  |
| Napapar         | PNG       | East New Britain       | 412                                                         | 391                                                  |
| Wirui           | PNG       | East Sepik             | 1382                                                        | 1313                                                 |
| Total           |           |                        | 17,160                                                      | 16,302                                               |

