The model will include time (month) as a continuous variable, a binary variable for the implementation intervention (see (a) and (b) above), an interaction between elapsed time (since implementation) and the implementation, seasonal variation in malaria (captured using splines), adjusted for potential time-varying confounding variables including large scale malaria control activities outside of the SCOPE study and unexpected antimalarial stock outages, and allowing for a random effect for intercept to account for clustering by health facility site (Turner SL et al. 2021).

For the effectiveness outcome S2.SE15, monthly incidence of symptomatic *P. vivax* malaria will be calculated using clinic catchment populations provided by health facilities (or if not available, the most recent census). Incidence rate ratios (IRRs) (95% CIs) for the intervention effect will be estimated from a negative binomial regression model fitted to the monthly aggregated data.

**Figure 2.** Example impact model for the implementation package on the effectiveness outcome measure S2.SE15 (incidence of symptomatic *P. vivax* malaria infections). An impact model with an immediate change in level and slope. While immediate level change is allowed to occur in this model at the time of implementation, the estimand of interest with regards to level change will be calculated 6 months after implementation (at 12 months) relative to the implementation timepoint (at 6 months).

[figure not shown]

For comparison of outcomes S2.SE16 (the proportion of febrile patients with asexual *P. vivax* parasitaemia by microscopy) and S2.SE14 (the proportion of patients with severe anaemia (haemoglobin < 7 g/dl), determined from cross-sectional surveys in the pre- and post-implementation periods), prevalence ratios (95% CIs) for the intervention effect will be estimated from log-binomial regression models, and if there are convergence issues, Poisson regression with robust variance will be performed (Barros AJD & Hirakata VN 2003).

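### The SAP does not fix one variance method for S2.SE15 and states no remedy for autocorrelation or for shared shocks among the four Timika clinics, so its intervals may be too narrow

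*SAP*

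**What the plan says.** Four places in the SAP bear on the standard errors for S2.SE15.

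- Section 9.2 describes a segmented regression, with incidence rate ratios "estimated from a negative binomial regression model fitted to the monthly aggregated data", "allowing for a random effect for intercept to account for clustering by health facility site". No slope term by facility and no locality level is named there.
- The Clustering paragraph that follows says clustering in the effectiveness outcomes will be explored "using either random effects or robust standard errors for clustering by health facility". It gives no rule for choosing between the two.
- Section 9.3, Heterogeneity: "The mixed effects models allow for some heterogeneity in slope and intercept at the health facility level".
- Section 9.3, Autocorrelation: autocorrelation "will be assessed visually by plotting the residuals (difference between observed and model predicted outcome) over time for each model". No test, threshold or consequence follows.

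SAP Table 1 places Timika, Bhintuka, Pasar Sentral and Wania in the same locality; the Pasar Sentral row, for example, reads "Timika, Southern Papua | 4937". Section 10 lists the S2.SE15 sensitivity analyses. They change the inclusion of Stage 1 data and the seasonality term, and neither bears on dependence between observations.

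**The concern.** A facility random intercept absorbs stable differences in level between clinics. It does not absorb a run of high or low months within a clinic, or a month that is high in several clinics of one town at once. Section 9.3 presents itself as measures to adjust for autocorrelation but offers only a diagnostic.

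The diagnostic is also weak. With 12 months before and 12 after, the approximate standard error of a lag-1 autocorrelation in one facility is 1/√24 = 0.20, so a value of 0.3 is hard to see by eye.

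The three descriptions of the variance structure can give different intervals from the same data, and the choice is left open until the data are in hand. S2.SE15 is the plan's incidence measure of effectiveness in a study meant to inform national policy. Overstated precision would make ordinary fluctuation, much of it possibly from one town, look like an effect of the package.

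**Working it through.** **1. The plan's own figure.** SAP section 4.2.1 states 89.3% power at 70% recruitment. Inputs: difference 135.8 × 0.6 × 0.3 × 0.7 = 17.11 cases per month, SD of the difference 15, n = 10 clinics, two-sided alpha 0.05. The noncentrality is 17.11/(15/√10) = 3.61 on 9 df, which gives 89.3%. The figure reproduces, and so do the other five rows of Table 2. The calculation treats the ten clinics as independent. If the four Timika clinics behaved as a single unit (n = 7, same SD), the noncentrality is 17.11/(15/√7) = 3.02 on 6 df and power is 71.2%. That is a bound, not an estimate.

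**2. Timika's share.** Episodes: 3173 + 1164 + 4937 + 3681 = 12,955; 12,955/17,160 = 75.5%. This is a share of cases. In a negative binomial model, a clinic-month with mean μ carries information roughly μ/(1 + αμ), where α is the dispersion. Summing over clinics with μ = annual episodes/12, Timika's share is 75.5% at α = 0, 57% at 0.01, 46% at 0.05 and 43% at 0.1. The SAP gives no α.

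**3. Coverage with model-based errors.** Settings: 400 null datasets per scenario, Table 1 volumes, 12 + 12 months, negative binomial segmented model, facility intercepts (fitted as fixed effects in place of random intercepts) and country-specific seasonality. Assumed, because the SAP is silent: month-to-month log-scale SD 0.2, lag-1 correlation ρ, and share of variance common to the Timika clinics. Coverage of nominal 95% intervals:

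| ρ | Shared in Timika | Month-6 effect | Slope change |
|---|---|---|---|
| 0 | none | 94.8% | 93.5% |
| −0.2 | none | 95.0% | 95.8% |
| 0.3 | none | 89.8% | 87.8% |
| 0 | half | 87.0% | 88.8% |
| 0.3 | half | 85.5% | 78.0% |
| 0.6 | half | 78.5% | 63.8% |

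With positive autocorrelation, a shared shock or both, the true standard error was 1.18 to 1.56 times the model's for the month-6 effect and 1.20 to 2.12 times for the slope change.

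**4. Type I error by choice of standard error.** Further null datasets at log-scale SD 0.2 compared the two options the SAP allows.

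- Model-based errors, independent months: about 5–7%.
- Model-based errors, ρ = 0.3 to 0.5, nothing shared: 8–12% (month 6) and 11–21% (slope).
- Model-based errors with a shared Timika shock: 13–20% (month 6) and 13–36% (slope).
- Facility-clustered errors: about 4–5% under serial correlation alone, but still 9–12% with the shared shock.

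The open choice in the Clustering paragraph therefore matters. One option deals with serial correlation and the other does not. Neither fully deals with correlation across clinics.

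**5. Slope heterogeneity.** With independent months, a facility slope SD of 0.02 per month gave coverage of 94.8% and 96.0%; a facility intervention-effect SD of 0.15 gave 92.5% and 95.2%. Serial and shared correlation drive the problem, not missing random slopes.

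**The case against.** The best defence is that the plan is less bare than section 9.2 alone suggests. The Clustering paragraph permits facility-robust errors, which largely repair within-clinic serial correlation. The model also adjusts for seasonality by splines, separately for Indonesian and PNG sites, and for large control activities and stock outages; section 10 adds a site-specific rainy/dry variable. Much of what would strike all four Timika clinics together is therefore modelled, and only the unmeasured remainder is shared. The case share also overstates Timika's weight once counts are overdispersed. Finally, S2.SE15 is one of 18 Stage 2 secondary endpoints and is reported as estimates with 95% intervals, without a significance-based decision rule.

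All of this stands and limits the point. It does not remove it. The robust option is permitted but not chosen, and it does not reach correlation between clinics. The covariates do not capture an unusual wet season, population movement or persistent transmission. An interval that is too narrow misleads whether or not a test is attached.

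A reader might also infer that the same model and errors will be reported whatever the residual plot shows. The SAP does not say so; it is silent on what follows the plot.

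**Conclusion.** The variance method for S2.SE15 is not fixed, autocorrelation has a check but no remedy, and dependence among the four Timika clinics is not addressed. That much is read directly from the document.

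The consequence is conditional. If residuals are positively autocorrelated, or the Timika clinics share shocks beyond what is modelled, intervals from the random-intercept model with model-based errors may be too narrow. With log-scale SD 0.2, lag-1 correlation 0 to 0.5 and half of Timika's variance shared, type I error is about 8–20% for the month-6 effect and 11–36% for the slope change, against about 5–7% under independence. These figures are a range under assumptions.

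It is tempting to say flatly that the intervals are too narrow, or that chance swings in one town will be reported as a significant effect across two countries. The document supports neither. It gives no residual or between-clinic correlation, and coverage is close to nominal when both are absent. Larger assumed shocks would push the error rates higher, but nothing in the SAP justifies choosing them. The change is worth making before the analysis and is inexpensive.

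**What to change.** - Make section 9.2, its Clustering paragraph and the Heterogeneity paragraph of 9.3 state the same single primary method for S2.SE15. It should allow for serial correlation regardless of what the plot shows. Examples are an AR(1) term within facility, or facility-clustered standard errors with a small-sample t correction for 10 clusters.
- Add to section 10 a prespecified S2.SE15 sensitivity analysis with a month random effect shared by the four Timika clinics.
- Keep the residual plot as a check on the chosen model.

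Two other remedies are not recommended. Random facility slopes for time and intervention would be hard to support with ten facilities, and slope heterogeneity was not the source of the inflation. Resampling whole localities is unreliable with only seven of them: simulated percentile intervals rejected 16% and 13% of the time with fully independent months, where 5% is nominal.

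The cost is a revision of SAP wording, a slightly more complex model and somewhat wider intervals.

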## **10 Sensitivity Analyses**

The following sensitivity analyses will be performed for the analysis of the S2.SE15 effectiveness outcome (incidence symptomatic *P. vivax* malaria episodes);

- The analysis will include incidence data from stage 1 implementation in addition to stage 2 in the post-implementation period for the ITS analysis (Appendix 4: Figure 2).
- The analysis will be performed with alternative adjustments for seasonality
  - Adjustment with a categorical rainy/dry seasonality variable derived specifically for each site

The following sensitivity analyses will be performed for the analysis of the S2.SE18 effectiveness outcome (cumulative risk of recurrence);

- The analysis will be restricted to Indonesian patients who have a malaria card number recorded. It is thought that patients without a malaria card no. in Indonesia tend to be part of a more transient population with different health-seeking behaviours.

## **11 Exploratory analyses comparing patients enrolled and not enrolled in SCOPE**

The impact of the intervention on the risk of recurrence is assessed by Endpoint S2.SE17. At the start of Stage 2, it was apparent that the total sample size enrolled into the SCOPE study would be lower than anticipated. Additional analyses were added to the SAP to explore this endpoint with new endpoint S2.SE18.

S2.SE18: Cumulative risk of representation to the same health facility with symptomatic *P. vivax* malaria within 6 months in patients enrolled and not enrolled into the SCOPE Study. Comparisons made in the Post-Implementation Stage only.

### Dataset for Analysis

Endpoint S2.SE18 will include all SCOPE patients eligible for PQ treatment and a selected dataset of non-SCOPE patients who were treated with PQ treatment for *P. vivax* malaria according to national guidelines. SCOPE patients from both stage 1 and stage 2 will be included. The non-SCOPE patients will be eligible for selection if they were not enrolled in SCOPE at any stage (based on malaria card number and other identifying factors) and were administered the PQ dose according to national guidelines and met the SCOPE eligibility criteria: age >1 year (PNG) or ≥6 months (Indonesia, haemoglobin concentration ≥8 g/dl, and not pregnant or lactating and did not have severe malaria. Day 0 for non-SCOPE patients will be taken as the first visit by a patient following the stage 1 implementation date.

In the scenario that the baseline characteristics differ substantially between the SCOPE and non-SCOPE patients, a subgroup of these non-SCOPE patients will be selected for analysis using propensity score matching with the SCOPE patients. This will be done separately by country (PNG and Indonesia) and will be based on the following variables:- age, sex, body weight. Propensity score matching is a valuable way to control for bias and achieve pseudo randomisation in this exploratory analysis which is comparing SCOPE patients to routinely collected patient data.

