#### 4.2.1 Revised and corrected Stage 2 power and precision calculations

Assumptions underlying the following Stage 2 power calculations include the following:

1. 5% of patients are ineligible for the intervention package (pregnancy, lactation, severe malaria, age <6m (Indonesia) or <1 yr (PNG)).
2. The impact on the risk and rate of infection will be the same across different endemic sites.
3. The mean baseline risk of *P. vivax* recurrence at 6 months is 20%
4. Loss to follow-up in both groups is 10%
5. Alpha = 0.05

During the 12-month pre-implementation period, a total of **17,160** patients with *P. vivax* (mono or mixed infections) presented to the ten study clinics (see Table 1). Assuming 5% of patients are ineligible for enrolment due to pregnancy, lactation or age under 6 months (Indonesia) or 12 months (PNG), this gives an estimated maximum number of patients eligible for recruitment into Stage 2 of **16,300**.

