| 0.5                                                               | 8,150                                   | 135.8                                                           | 12.22                                  | 123.58                                                            | 63.2%                                         |

**Example STATA code:** power pairedm 135.8 111.36, sddiff(15) n(10) alpha(0.05).

Based on previous estimates, 60% of cases of *P. vivax* malaria seen at each clinic are due to relapse and therefore preventable with improved radical cure. We predict the intervention package will reduce the individual risk of relapse by 30%. With anticipated recruitment of 70% of eligible patients, the total predicted sample size in Stage 2 would fall to **11,410** patients receiving primaquine over 12 months of enrolment. Based on this lower predicted enrolment and using the assumptions as above, the predicted absolute reduction in incidence at each clinic would be 17.11 cases per month  $((135.8 \times 0.6) \times 0.3 \times 0.7)$  and resultant power to detect this difference would be **89.3%**.

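### S2.SE18 drops comparator patients who enrol in SCOPE after Day 0, which deletes non-SCOPE recurrences and biases the comparison against SCOPE

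*SAP*

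**What the plan says.** Section 11 of the SAP compares the cumulative risk of returning to the same facility with symptomatic P. vivax "within 6 months in patients enrolled and not enrolled into the SCOPE Study". Its Dataset for Analysis subsection sets these rules:

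- Comparator: "The non-SCOPE patients will be eligible for selection if they were not enrolled in SCOPE at any stage", with enrolment looked up "based on malaria card number and other identifying factors". They must also have received primaquine under national guidelines and met the SCOPE eligibility criteria.
- Comparator time zero: "Day 0 for non-SCOPE patients will be taken as the first visit by a patient following the stage 1 implementation date".
- SCOPE group: all SCOPE patients eligible for primaquine, and "SCOPE patients from both stage 1 and stage 2 will be included". No Day 0 is stated for them.
- Period: "Comparisons made in the Post-Implementation Stage only".

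Matching, if used, is on age, sex and body weight. The Cox model adjusts for calendar time and seasonality, or for age, sex and weight when matching is not used, with a shared frailty for facility. The only S2.SE18 sensitivity analysis (Section 10) restricts to Indonesian patients with a recorded malaria card number.

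**The concern.** Comparator membership is decided partly by what happens after time zero. SCOPE enrols patients when they present with P. vivax, so a patient not enrolled at Day 0 can enrol later only by presenting again. If that happens at the same facility within six months, the enrolment visit is itself the S2.SE18 event. The patient leaves the comparator and the event goes too. The person may then re-enter as a SCOPE patient, with the recurrence as the index episode.

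The comparator's recurrence risk is therefore understated, and an effective package could look weaker than it is, useless or harmful. Matching and Cox adjustment cannot restore deleted events. Incomplete linkage does not help either: a comparator recurrence is counted only if the two visits are linked, and that link also reveals an enrolment at the second visit.

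The Day 0 wording adds a second difficulty. Only four of the ten facilities ran Stage 1 (Section 3.1.1). At the other six, the Stage 1 implementation date is either undefined or falls before their own implementation. Patients seen there in that interval could not have been enrolled, so they are not refusers and might well enrol on returning in Stage 2.

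**Working it through.** **Inputs.** Section 4.2.1 gives a mean six-month recurrence risk of 20%, 10% loss to follow-up and alpha 0.05. It predicts a 30% reduction in individual risk of relapse, and Table 3 uses HR 0.7, 0.8 and 0.9. The share q of re-presenting non-SCOPE patients who enrol at that visit is not given, so a range is shown.

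**The plan's own figure.** S2.SE18 has no power figure. The nearest is Table 3 for S2.SE17: 92% power for HR 0.9 with 11,410 patients per period. Exponential event times with competing 10% loss give 4,144 events. The Schoenfeld formula gives z = (√4,144 / 2) × |ln 0.9| − 1.96 = 1.43, a power of 92.4%. The HR 0.9 column reproduces throughout (98.2, 97.0, 95.2, 92.4, 88.1, 81.8% against 98, 97, 95, 92, 88, 82%), so the recurrence inputs are understood as intended.

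**Effect of the rule.** Let r = 0.20 be the true comparator risk. The rule deletes a fraction rq of the comparator, all of them patients with events:

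observed comparator risk = r(1 − q) / (1 − rq)

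On the risk scale the SCOPE risk is 0.20 × 0.7 = 14%. On the hazard scale it is 1 − 0.8^0.7 = 14.5%, and the observed HR is ln(1 − SCOPE risk) / ln(1 − observed comparator risk).

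| q | Observed comparator risk | Risk ratio (true 0.70) | HR, closed form (true 0.70) | 0.70/(1 − q) |
|---|---|---|---|---|
| 0 | 20.0% | 0.70 | 0.70 | 0.70 |
| 0.10 | 0.18/0.98 = 18.4% | 0.76 | 0.77 | 0.78 |
| 0.30 | 0.14/0.94 = 14.9% | 0.94 | 0.97 | 1.00 |
| 0.50 | 0.10/0.90 = 11.1% | 1.26 | 1.33 | 1.40 |
| 0.70 | 0.06/0.86 = 7.0% | 2.01 | 2.16 | 2.33 |

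The last column is what a simulation shows (400,000 patients per scenario, constant hazard, entry over 12, 18 or 24 months). It also deletes patients who enrol after month 6, and agrees to within about 0.02.

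**Break-even.** On the risk scale, 0.14(1 − 0.2q) = 0.2(1 − q) gives q = 0.06/0.172 = 0.35. On the hazard scale it is 0.32, or 0.31 to 0.36 for baseline risks of 10 to 40%. With post-month-6 deletions included it is about 0.30. For true HRs of 0.8 and 0.9 the closed-form break-even falls to 0.22 and 0.11.

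**Persistent non-enrollers.** Suppose some non-enrolled patients never enrol and the rest have q = 0.7. If 70% never enrol, the average q is 0.3 × 0.7 = 0.21, the observed comparator risk is 0.158/0.958 = 16.5%, and the HR is about 0.87 (simulated about 0.86). If 50% never enrol, the simulated HR is about 1.0; if 30%, about 1.3.

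**With eligibility fixed at Day 0** and the re-presentation counted as the event, the simulated HR returns to the truth (about 0.70, 0.90 and 1.00) at every q tried.

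**The case against.** - *Exploratory status.* Section 11 is titled exploratory, and it says the effect on recurrence is assessed by S2.SE17. Neither S2.SE17 nor the primary endpoint S2.PE1 uses this rule. That limits the severity. It does not excuse the rule, because Section 2.2.2 lists S2.SE18 among the secondary endpoints.
- *Direction.* The bias runs against SCOPE and cannot create a false claim of benefit. True, but a false null or apparent harm also misleads.
- *q is unknown.* A reader might take the planned 70% recruitment as q and conclude that the observed ratio would be about 2. The documents do not support that. The 70% applies to all eligible patients, not to those already not enrolled once, who may include refusers and transient patients.
- *Non-events are deleted too.* A reader might infer that comparators without an event are never dropped. In fact, those who enrol after month 6 or at another facility are dropped as well. The simulation shows that post-month-6 deletions do not offset the bias under a constant hazard; deletions at other facilities were not modelled.
- *Day 0.* A reader might infer that pre-implementation visits are definitely included at six facilities. The text does not say whether the date is common or facility-specific, and Section 11 restricts the comparison to the post-implementation period. This is an ambiguity to reconcile, not an established contradiction.
- *Purpose and visibility.* The exclusion keeps one person from appearing in both groups, a legitimate aim that the fix must handle. The planned flowchart will show reasons for ineligibility, but it does not correct the estimate or have to separate enrolment before Day 0 from enrolment after it.

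**Conclusion.** The comparator rule is wrong as written. It conditions on enrolment after Day 0, which within six months at the same facility coincides with the endpoint event, and it biases the comparator risk downward. Nothing in Sections 10 or 11 repairs this.

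The size rests on an assumed q. With 20% baseline risk and 14% SCOPE risk, a true ratio of 0.70 is observed as 0.76 to 2.01 for q from 10% to 70%. Reversal needs q above about 0.35 (about 0.32 on the hazard scale). If most non-enrolled patients never enrol, the result is attenuation, to about 0.86 in the case shown. Reversal is therefore possible but not established. The point does not touch S2.PE1 or S2.SE17 and ranks below a defect in either, but it should be corrected before S2.SE18 is analysed.

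**What to change.** Amend Section 11, Dataset for Analysis:

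1. Define non-SCOPE status at the index visit only: not enrolled in SCOPE on or before Day 0.
2. Count a P. vivax re-presentation to the same facility within six months as the event, whether or not the patient enrols at that visit.
3. Censor at a later SCOPE enrolment that is not itself the event, such as one at another facility.
4. Keep all SCOPE patients, with Day 0 stated as enrolment. Let a person contribute a non-SCOPE and then a SCOPE episode, with person-level robust standard errors.
5. Replace the Stage 1 implementation date with each facility's own implementation start date, so that Day 0 agrees with the restriction to the post-implementation period.
6. Report in the flowchart how many comparator patients enrolled after Day 0, split by whether that visit was the event.

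The cost is SAP wording, re-derivation of the comparator from data already held, and handling of people who appear in both groups. No new data are needed.
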